| OQUA      | Otology Questionnaire Amsterdam                                                                                                                                                                                        |

|                   |                                                                                                                                                                                                                                                                                                                                                  |
|-------------------|--------------------------------------------------------------------------------------------------------------------------------------------------------------------------------------------------------------------------------------------------------------------------------------------------------------------------------------------------|
| PROM       | Patient-reported outcome measure                                                                                                                                                                                                                                                                                                          |
| PSA        | Probabilistic sensitivity analysis                                                                                                                                                                                                                                                                                                        |
| Recidivism | Total number/rate of residual and recurrent disease                                                                                                                                                                                                                                                                                       |
| (S)AE      | (Serious) Adverse Event                                                                                                                                                                                                                                                                                                                   |

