All pre-operative measurements are part of standard care in the Netherlands and Belgium. Pre-operatively patients receive an audiometric exam, a physical examination of the ear, a CT-scan and fill in the patient-reported outcome measure (PROM). Follow-up will be planned at least at 6-18 weeks, at around 1 year and at around 3 years after surgery. It is important to note that conducting a CT scan and audiometry preoperatively as well as the DW-MRI's after 1 and 3 years are part of the standard care. In line with standard care, if there is a suspicion for recurrent or residual pathology (either clinically by micro-otoscopy or radiologically by DW-MRI) the treating physician will perform a revision surgery. If during revision surgery the suspicion is confirmed, the type of recidivism (residual or recurrent) is recorded and the follow-up of the patient ends. Data that is collected up until the point of detection of residual or recurrent disease will be used for analysis (this is not an exclusion criterium). If the suspicion is not confirmed (false-positive) then the patient will continue the follow-up as planned (unless a reconstructive procedure with the goal of improving hearing has been performed). During the three years of follow-up, patients should not undergo another type of ear surgery. If this is unavoidable, as judged by the treating physicians, the patient will be retrospectively excluded. In order to ensure that the same surgical data is collected in all participating centers, a standardized operation report will be written and shared by the sponsor (UMC Utrecht). This operation report will be recorded in the electronic patient dossier (with the exception of the information if obliteration was used or not) and transferred to Castor EDC. In Castor there will be a variable to also record if obliteration has taken place or not. The only methodology that is different to standard care is the randomization of the patients and the completion of the questionnaire. It is important to note that the technique used for the obliteration technique differs slightly between centers. The exact surgical technique will be described by the participating otologists and included in the description of the study, for example in a publication.

**Figure 1.** Flowchart of the study. *Standard care is indicated by \**[figure not shown]

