#### 4.4 Sample size calculation

To detect a clinically relevant outcome of the primary objective (residual or recurrent disease) a sample size of at least 160 participants is needed. To calculate the sample size we used applicable and recent retrospective results of the UMC Utrecht (from January 2015 to March 2020) and reported recurrence rates from a systematic review of the literature, as this represents the most methodologically comparable and robust dataset currently available. We used our results to calculate the sample size needed with a power of 0.80. Relevant clinical difference was set at 20%. The calculation is based on a two independent proportions power analysis using a Z test with pooled variance with a alpha of 0.05 and a power of 0.80. Sample size calculations were performed with PASS 2008 and resulted in 80 patients per arm. To compensate for potential dropouts, a 10% margin is implemented, **resulting in 178 patients in total.**

| Two Independent Proportions (Null Case) Power Analysis                    |                               |                               |                                     |                                   |                     |                     |                 |                 |        |
|---------------------------------------------------------------------------|-------------------------------|-------------------------------|-------------------------------------|-----------------------------------|---------------------|---------------------|-----------------|-----------------|--------|
| Numeric Results of Tests Based on the Difference: P1 - P2                 |                               |                               |                                     |                                   |                     |                     |                 |                 |        |
| H0: P1-P2=0. H1: P1-P2=D1<>0. Test Statistic: Z test with pooled variance |                               |                               |                                     |                                   |                     |                     |                 |                 |        |
|                                                                           | Sample
Size
Grp 1
N1 | Sample
Size
Grp 2
N2 | Prop H1
Grp 1 or
Trtmnt
P1 | Prop
Grp 2 or
Control
P2 | Diff
if H0
D0 | Diff
if H1
D1 | Target
Alpha | Actual
Alpha | Beta   |

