### **8.1 Primary study parameter(s)**

The data of our primary outcome are quantitative and will be presented as frequencies and proportions. To compare the difference in recidivism (recurrent and residual disease) at 12, 36 and 60 months between both surgical groups the Chi-squared test or Fisher's exact test will be used. The relative risk (RR) and absolute risk difference (RD) will be calculated as effect sizes using a generalized linear model for binomial outcome with a log-link (for RR) and identity link (RD). The primary analysis will be adjusted for site by including centre as covariate in a logistic regression model with treatment arm as the main predictor. All effect sizes will be accompanied by 95% confidence intervals. To graphically demonstrate the rates of recidivism, recurrent and residual disease over the follow-up time, a Kaplan-Meier analysis will also be performed and survival curves will be constructed. Multiple imputation will be used to deal with missing

outcomes. A 20% difference is defined as the threshold for clinical relevance and will be consistently applied in both clinical effectiveness analyses and the health economic evaluation.

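### Section 8.1 plans Kaplan-Meier curves for recurrent and for residual disease, which are competing events here because follow-up ends at the first confirmed type; cumulative incidence curves are the suitable display

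*Protocol*

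**What the plan says.** Section 8.1 plans, beside the main comparison, a time-based display: "To graphically demonstrate the rates of recidivism, recurrent and residual disease over the follow-up time, a Kaplan-Meier analysis will also be performed". The list has three items: the composite and its two components. The abbreviations list defines recidivism as "Total number/rate of residual and recurrent disease".

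Section 3 says what happens when a suspicion is confirmed at revision surgery: "the type of recidivism (residual or recurrent) is recorded and the follow-up of the patient ends". It adds: "Data that is collected up until the point of detection of residual or recurrent disease will be used for analysis". A patient whose suspicion is not confirmed normally stays in follow-up.

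The main comparison in section 8.1 concerns recidivism as a whole at 12, 36 and 60 months. It uses a chi-squared or Fisher test, relative risk and risk difference from binomial models, and a logistic model adjusted for centre. The protocol mentions no cumulative incidence function or other competing-risk method.

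**The concern.** Once one type is confirmed, the other is no longer looked for in that patient. A standard Kaplan-Meier curve for recurrent disease therefore censors patients at confirmed residual disease, and the reverse. Censoring treats them as still able to show the other type later, at the same rate as patients still under observation. One minus that curve describes a setting in which the other type does not occur. It is not the proportion of patients found with the type in question, yet section 8.1 says the curves are to show rates.

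The primary objective in section 2 names both recurrence and residual rates. Section 1 describes the purpose of obliteration as stopping retraction and so lowering recurrence, while its opponents worry about disease left behind. Readers will therefore look at the two types separately. Two component curves that do not add up to the recidivism curve would also disagree with the frequencies and proportions in the same report.

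**Working it through.** **The plan's own figure.** Section 4.4 assumes recidivism of 40% (control) and 20% (obliteration) and uses a "Z test with pooled variance with a alpha of 0.05 and a power of 0.80", which "resulted in 80 patients per arm". Exact binomial enumeration of that test at 80 per arm gives power 0.8009, the stated value. With the 10% margin, 160 / 0.9 = 177.8, so 178. The planning rates are thus confirmed as the basis of the design and are used below.

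**Inputs.**
- Total recidivism F: 0.40 and 0.20 (section 4.4).
- DW-MRI at about 1, 3 and 5 years (section 6.1.1).
- Share s of one type: not given for these rates, so assumed. Base case 0.5, then varied.
- Share of events found at each scan: not given, so assumed 40/40/20%.
- No other dropout.

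**Events found at the three scans, equal split.** The type-specific curve is the product over scans of (1 − events of that type / patients still at risk).
- Control: 0.08, 0.08 and 0.04 of each type; at risk 1, 0.84 and 0.68. 1 − KM = 1 − 0.92 × (1 − 0.08/0.84) × (1 − 0.04/0.68) = 1 − 0.92 × 0.9048 × 0.9412 = 0.2166. The true rate is 0.20.
- Obliteration: 0.04, 0.04 and 0.02; at risk 1, 0.92 and 0.84. 1 − KM = 1 − 0.96 × (1 − 0.04/0.92) × (1 − 0.02/0.84) = 1 − 0.96 × 0.9565 × 0.9762 = 0.1036. The true rate is 0.10.
- Sum of the two types: 43.3% against 40%, and 20.7% against 20%.
- Gap per type: 21.66 − 10.36 = 11.3 points against 10.

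Other assumed timings (equal thirds, 50/30/20%, 20/40/40%) give an excess of 1.57 to 1.68 points in control and 0.35 to 0.37 with obliteration.

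**Continuous time, proportional hazards for the two types.** The cumulative incidence is sF, and 1 − KM = 1 − (1 − F)^s.
- Control: 1 − 0.6^0.5 = 0.2254, so 22.5% against 20% (sum 45.1%).
- Obliteration: 1 − 0.8^0.5 = 0.1056, so 10.6% against 10% (sum 21.1%).
- Gap per type: 12.0 points against 10.

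**Sensitivity to the split.** A 25:75 split in both arms gives an excess of 1.8 to 2.0 points (control) and 0.4 (obliteration) in continuous time, and about 1.2 to 1.3 and 0.3 at the scans. The only split in the protocol is 0.28% recurrent to 4.2% residual, for canal wall up surgery with obliteration (section 1). Applied to both arms as an assumption, with 40/40/20% timing, recurrent disease in control totals 2.5% and reads 1 − 0.99 × (1 − 0.01/0.84) × (1 − 0.005/0.68) = 2.9%, an excess of 0.4 points. In the obliteration arm the excess is about 0.1.

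**Where the pattern breaks.**
- Order of events: suppose that in the 40% arm all residual disease (20%) is found at the first scan, and recurrent disease (10% and 10%) at the next two. Residual then reads correctly at 20%. Recurrent reads 1 − (1 − 0.10/0.80) × (1 − 0.10/0.70) = 25% against 20%.
- Order of arms: in continuous time, with control split 38:2 and obliteration 10:10, the excess is 0.45 and 0.52 points in control and 0.56 in obliteration. The arm with fewer events then has the larger excess.

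**The case against.** The strongest answer is that no planned inference uses these curves. The endpoint, sample size, test and effect measures all concern the composite, and Kaplan-Meier enters only as an added graphic. No log-rank test, hazard ratio or type-specific comparison between arms is planned. This stands and settles the rank of the point. A reader might infer that the primary result is biased; the documents do not support that, because a composite Kaplan-Meier curve does not have this problem and the primary test, relative risk and risk difference do not use the curves.

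A reader might also infer that both types are always overstated, always more so in the arm with more events, so that the apparent benefit of obliteration is always enlarged. The two counter-examples in the working show that this is not general. It holds for the common splits and timings tried.

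The size is small against sampling error. With 80 per arm, a rate of 20% has a 95% half-width of 1.96 × √(0.2 × 0.8 / 80) = 8.8 points, and the difference 20% v 10% one of 1.96 × √(0.16/80 + 0.09/80) = 11.0 points. That is fair, but the error is systematic and avoidable.

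Section 8.1 states no censoring rule. Keeping patients with the other type in the risk set to 60 months would, without other dropout, return the crude cumulative proportion. Such detail could sit in a statistical analysis plan. But the protocol names an estimator whose standard use does not give two of the three rates listed, which is more than a missing detail.

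Finally, the sentence could be read as describing one composite curve, since the same section elsewhere explains recidivism by naming both types in brackets. The three-item list and the plural curves favour separate ones, and on the other reading the wording still needs clearing up.

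**Conclusion.** The point holds as a minor correction to a descriptive display. Follow-up ends at the first confirmed type, so a standard type-specific Kaplan-Meier curve does not estimate the rate that section 8.1 says it will show.

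At the planning rates, with an equal split and detection at the three scans, the excess is about 1.7 points per type in the 40% arm and 0.4 in the 20% arm, and the gap per type reads 11.3 points instead of 10. Continuous time with proportional hazards gives 2.5 and 0.6 points. Uneven splits give less under the same timing; strict ordering of the two types can give more for the later type and nothing for the earlier one. Split and timing are assumptions, because the protocol gives neither for its planning rates. What does not depend on the chosen split is that a type is overstated when events of the other type precede it, and that the two curves then sum to more than total recidivism.

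**What to change.** In section 8.1, limit Kaplan-Meier to combined recidivism. State that recurrent and residual disease will each be shown by arm as a cumulative incidence curve (Aalen-Johansen estimator), with the other type as a competing event. The two curves then add up to total recidivism and agree with the tabulated proportions when there is no other dropout.

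The cost is one sentence in the protocol and a standard routine outside the SPSS Kaplan-Meier procedure. No new data are needed: type and detection are already recorded. Sample size and primary analysis stay as they are.

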## 8.2 Secondary study parameter(s)

### Differences in STAMCO

- Within the STAMCO classification groups (STAM 1,2,3) the Chi-square test will be used to assess the differences in recidivism.

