**Secondary Objective(s):**

- Hearing outcomes
- Health-related quality of life
- Describing localization and disease extension using the STAMCO classification
- Health economic cost analysis
- Comparing any differences in patient and surgical characteristics

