#### 6.1.2 Secondary study parameters/endpoints

- **Baseline characteristics:**
  - Patient demographics (age (as collected by birthyear), gender), date of first presentation at the outpatient clinic, date of surgery, operated side (right/left), applied antibiotic treatment within in 2 weeks prior to surgery.
  - Co-morbidities and lifestyle factors: smoking, obesity, asthma, diabetes, COPD, allergies, rhinosinusitis.
  - Amount and type of all previous ear surgeries which are not mentioned in the exclusion criteria.
- **Hearing outcome:**
  - As measured by audiometric testing (pure-tone average thresholds (PTA) as calculated over 0.5, 1, 2 and 4 kHz for the air-conduction (AC) and bone-conduction (BC) and speech audiometry. This will be measured before the surgery, and at 6-18 weeks and around 1 year after surgery. The pre-operative audiogram should not have been measured more than 6 months prior to surgery.

- **Surgical characteristics:**

- A short 'standard' surgical report/template written by the participating otologists per center will be collected and used in the scientific publication to demonstrate any potential differences in surgical technique. This **does not** include patient information.
- STAMCO-classification: Localization and extension of the cholesteatoma, presence of preoperative complication status and the ossicular chain status before/at the time of removal of the cholesteatoma will be recorded. Any differences in outcomes in STAMCO classifications between the two randomized groups will be evaluated and described.

**Figure 2:** Localization, disease extension and complications as described by the STAMCO classification (18, ten Tije et al.)

[figure not shown]

- Material used for obliteration (Bonalive®, bonedust, hydroxyapatite, cartilage, muscle) as registered in the surgical report.

- Ossicular chain reconstruction (OCR); performed (yes/no), if yes, the used material and type of reconstruction (PORP, TORP, use of incus interposition, type 3 tympanoplasty) will also be reported.
- Surgical personnel: It is registered if an ENT-doctor in training (resident) or fellow has operated along with the specialist.
- Surgical time: Surgery time is recorded in minutes for each surgery and described.
- Revision surgery during follow-up: the information and observations as gathered by the surgical report will be collected from all revision surgeries performed during the follow-up of this study.
- **Complications**

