## **8. STATISTICAL ANALYSIS**

Data will be collected in Castor EDC and exported for Statistical analysis in IBM SPSS Data will be collected in Castor EDC and exported for Statistical analysis in IBM SPSS Statistics 29.0 (SPSS Inc., Chicago, IL, USA). Data will be presented according to the Consolidated Standards of Reporting Trials (CONSORT) Statement, an international guideline on adequate reporting of RCTs. To assess whether continuous variables are normally distributed, histograms and the Kolmogorov-Smirnoff test will be computed. Continuous data will be expressed as mean  $\pm$  standard deviation (SD) when normally distributed, and as median  $\pm$  interquartile range (IQR) when skewed. Number of cases and percentages will be presented for categorical variables. A p-value of less than 0.05 will be regarded as statistically significant for all calculations.

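### Separate chi-square tests within STAM stages cannot show whether the effect of obliteration differs by stage, and at the planned effect they will mostly give a mixed picture even if it does not

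*Protocol*

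**What the plan says.** The method for the STAMCO analysis is one sentence in protocol Section 8.2 (Differences in STAMCO): "Within the STAMCO classification groups (STAM 1,2,3) the Chi-square test will be used to assess the differences in recidivism". It names neither the groups compared nor the time point. Section 6.1.2 supplies the comparison: "Any differences in outcomes in STAMCO classifications between the two randomized groups will be evaluated and described". Arm versus arm within each stage is therefore the natural reading, though it is a reading. Section 2 words the matching secondary objective descriptively: "Describing localization and disease extension using the STAMCO classification".

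The opening of Section 8 sets the decision rule: "A p-value of less than 0.05 will be regarded as statistically significant for all calculations". The protocol states no arm-by-stage interaction, no test of homogeneity across stages and no caution on reading the within-stage p-values. The only interactions in Section 8.2 are arm by time point, for hearing and the OQUA.

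The trial is sized for the overall comparison only (Section 4.4): "Sample size calculations were performed with PASS 2008 and resulted in 80 patients per arm", for 20% against 40%.

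**The concern.** A significant result in one stage and a non-significant one in another is not evidence that the effect differs between them. Each stage holds only a fraction of a sample that has 80% power as a whole, so each test will often miss a real effect. Which stages cross 0.05 is then largely chance and stage size.

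The introduction criticises earlier research for rarely breaking outcomes down by extension and location, so results by stage are a likely output. A table that marks some stages significant and others not invites the reading that obliteration works in some stages only, and the planned tests cannot support or refute that.

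**Working it through.** **Inputs from the protocol.** Two-sided test ("H0: P1-P2=0. H1: P1-P2=D1<>0. Test Statistic: Z test with pooled variance"), alpha 0.05, 80 evaluable patients per arm, recidivism 20% with obliteration and 40% without (Section 4.4 and its table), 1:1 allocation stratified by centre only (Section 6.2).

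**Assumed.** The shares of STAM 1, 2 and 3, which the protocol does not give; several splits are tried, each equal between arms. The effect is taken as identical in all stages.

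**Step 1: reproduce the plan's figure.** The test statistic is z = (a/n − b/n) / √[p̄(1 − p̄)·2/n], with p̄ = (a + b)/(2n), rejecting when z² > 3.841, which is the uncorrected chi-square test. Summing the binomial probabilities of all (a, b) in the rejection region at n = 80 gives power 0.8009 and actual alpha 0.0472, both as in the protocol's table. The normal approximation gives power 0.794. Dropout: 160/0.90 = 177.8, so 178, also as stated.

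**Step 2: the same calculation within stages.** The stages are independent. With stage powers w1, w2, w3:

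- P(all significant) = w1·w2·w3
- P(none) = (1 − w1)(1 − w2)(1 − w3)
- P(mixed) = 1 − P(all) − P(none)

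For equal thirds (27/27/26 per arm):

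- all: 0.377 × 0.377 × 0.368 = 0.052
- none: 0.623 × 0.623 × 0.632 = 0.245
- mixed: 1 − 0.052 − 0.245 = 0.703

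| Patients per arm by stage | Power per stage | All | None | Mixed | No effect (40% in both arms): at least one significant |
|---|---|---|---|---|---|
| 27/27/26 | 0.377, 0.377, 0.368 | 0.052 | 0.245 | 0.703 | 0.139 |
| 16/40/24 | 0.252, 0.497, 0.333 | 0.042 | 0.251 | 0.707 | 0.152 |
| 48/24/8 | 0.586, 0.333, 0.144 | 0.028 | 0.236 | 0.736 | 0.166 |
| 8/64/8 | 0.144, 0.707, 0.144 | 0.015 | 0.214 | 0.771 | 0.183 |

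The last column is 1 − P(none) under no effect. The nominal value for three independent tests is 1 − 0.95³ = 0.143. Over other common recidivism rates the exact figure ranges from about 10% to 18%. If all 178 patients are evaluable, the mixed share at the planned effect is 71% to 81%.

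**Step 3: other uniform effects** (40% in the control arm, equal thirds):

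| Risk difference (points) | 0 | 10 | 15 | 20 | 25 | 30 | 35 |
|---|---|---|---|---|---|---|---|
| Mixed | 14% | 32% | 52% | 70% | 74% | 54% | 21% |

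The drop at 35 points depends on near-equal stages; with 8/64/8 the mixed share there is 90%.

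**Step 4: the alternative.** One homogeneity test across stages (log odds ratio, 2 degrees of freedom, 100,000 simulated trials) rejects in 3.4% of trials when the effect is uniform at 20% vs 40% with equal thirds, and in 1.6% to 3.4% over the splits tried. When the true risk differences are 0, 20 and 35 points, its power is 43% with equal stages and 8% to 31% with unequal ones.

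**The case against.** The strongest reply is that the protocol never says it will test or claim that the effect varies by stage. Sections 2 and 6.1.2 speak of describing, and a mixed set of p-values becomes an error only if someone draws the wrong inference from it. This stands in part. A reader might infer that the trial has committed itself to stage-specific efficacy claims, and the documents do not support that. But Section 8.2 prescribes hypothesis tests rather than description, and Section 8 labels each one significant or not. If description is the aim, estimates with confidence intervals serve it and the tests do not.

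A second reply is that interaction terms are commonly left to the statistical analysis plan, which is not at hand. The point here is the method the protocol does fix, which a plan that follows it would inherit.

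A third is that the interaction test is weak and that the model is large for about 80 × 0.20 + 80 × 0.40 = 48 expected events. That is true, and it is the reason to label stage results exploratory. It does not make three separate tests informative about differences between stages.

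A reader might also suspect that the chi-square test is invalid because of small counts. The protocol's figures do not show this. Expected counts use the pooled proportion, so 27 × 0.30 = 8.1 events per arm in an equal third. Only a smaller assumed stage falls below 5 (16 × 0.30 = 4.8).

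**Conclusion.** The point holds: the stated within-stage tests cannot show whether the effect differs by stage, and no test that could is stated. At the planned 20-point effect, uniform across stages with 80 per arm, a mixed pattern is the most likely result, at about 70% to 77% over the assumed splits. With no effect (40% in both arms), at least one stage is significant in about 14% to 18%.

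It would go too far to say that the analysis will usually suggest a difference whatever the truth. With equal stages, a mixed pattern is the majority result only for uniform effects of roughly 15 to 30 points; it falls to about 32% at 10 points and 14% at zero. The conclusion also rests on reading Section 8.2 as arm versus arm and on assumed stage shares. The analysis is secondary and the primary comparison is unaffected, so the change is advisable rather than critical.

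**What to change.** Replace the sentence in Section 8.2 with:

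> Recidivism is modelled by arm, centre, STAM stage and arm-by-stage interaction. The interaction p-value is reported. Stage-specific risk differences are shown with 95% confidence intervals, labelled exploratory, without separate significance claims.

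State the scale on which the interaction is tested, because the odds-ratio and risk-difference scales can disagree when the control risk varies by stage. For illustration, 40% to 20% is an odds ratio of (0.20/0.80)/(0.40/0.60) = 0.375. The same 20 points from an assumed 60% is (0.40/0.60)/(0.60/0.40) = 0.444. Section 8.1 already contains a logistic model with arm and centre and an identity-link model for the risk difference, so either can be extended once the choice is made.

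The cost is one sentence, with no new data, visits or patients. The downside is that the interaction test has low power, so a non-significant result would not show that the effect is the same in all stages.
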